### Sample Size

The sample size was calculated based on the primary outcome of BP. The effect size, widely used to measure treatment effects of continuous outcomes, is calculated as the difference between groups divided by the pooled SD. A previous meta-analysis, comparing mHealth intervention treatments with other traditional treatments, with the primary outcome being BP, reported an effect size of 0.7 [17]. Assuming α=.05, β=.2, and accounting for up to 20% attrition, a sample size of 68 is needed for this study.

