### Statistical Analysis

All analyses will be performed using SPSS. Continuous variables will be presented as mean and SD values. Categorical variables will be expressed as numbers and percentages. Independent samples *t* tests and chi-square tests will be conducted to assess the significance of differences in baseline characteristics or outcomes between the control group and intervention group at 3 time points: before the start of the intervention, 12 weeks after the intervention, and 1 year after the program. Paired *t* tests and McNemar's test will be used to compare the differences in some outcomes before and after the 3-month intervention, as well as before the trial and after the end of the program. A *P* value of less than .05 will be considered statistically significant.

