## Results

The study was funded in December 2021. The WHBDIP trial was approved by the Ethics Committee of Bengbu Medical College in June 2022 (2022-103) and registered in August 2022 (ChiCTR2200062643). Patient recruitment for those with hypertension started on September 5, 2022, and was completed on September 19, 2022. The 3-month intervention and phased data collection were completed in January 2023. Data analysis will commence in August 2023, and the final 1-year health outcome results will be collected in September 2023. We expect the primary outcomes to show changes in adherence indicators during the 3-month intervention, and health outcomes, including BP and other cardiovascular indicators, to change after the intervention and 1 year later. Furthermore, we will report on dropout rates and reasons for dropout during the trial.

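### Before-after paired tests share the P<.05 rule with the between-arm tests and are the only stated analysis of change; they should be descriptive, with efficacy resting on a baseline-adjusted comparison between arms

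*Protocol article*

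**What the plan says.** The Statistical Analysis section of the protocol article sets out two families of tests.

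- **Between arms.** Independent-samples t tests and chi-square tests assess "differences in baseline characteristics or outcomes between the control group and intervention group at 3 time points": baseline (T0), 12 weeks (T1) and 1 year (T2). No adjustment for the baseline value and no between-arm test of change is stated.
- **Before-after.** For the paired t and McNemar's tests, the plan is that they "will be used to compare the differences in some outcomes before and after the 3-month intervention". A second contrast, T0 against T2, is added in the same sentence: "as well as before the trial and after the end of the program". The outcomes are not named, and the arm or arms to be tested are not stated.

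One rule covers both families: a P "value of less than .05 will be considered statistically significant". Nothing ranks one family above the other.

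The Results section states the expectation as change: "We expect the primary outcomes to show changes in adherence indicators during the 3-month intervention". It then expects BP and other cardiovascular indicators to change after the intervention and at 1 year. It does not mention a difference between arms.

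The Sample Size section, by contrast, rests on a between-group quantity: the effect size "is calculated as the difference between groups divided by the pooled SD".

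**The concern.** A paired test compares patients with themselves. It answers whether an arm moved, not whether the intervention moved it. Three features of this trial make movement in both arms plausible.

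- The control group is not untreated. Under Intervention Procedure and Monitoring it receives oral education on exercise, diet, BP monitoring and regular medication.
- Recruitment ran from 5 to 19 September 2022 and the 3-month data were complete in January 2023, so the T0 to T1 contrast crosses from late summer to winter in both arms.
- Both arms are measured repeatedly, and some outcomes rely on self-report, as the limitations paragraph concedes.

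Regression to the mean is a weaker source here, because entry requires no BP threshold.

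A significant change in one arm beside a non-significant change in the other can look like an intervention effect, although the two arms have not been compared. At stake is how a published before-after P value would be read when it stands level with the randomised comparison and is the only planned analysis of change.

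**Working it through.** **1. Arm size.** The Sample Size section says: "Assuming α=.05, β=.2, and accounting for up to 20% attrition, a sample size of 68 is needed for this study", with an earlier meta-analysis that "reported an effect size of 0.7". For a two-sided two-sample t test at d = 0.7, α = .05 and power 0.80, the solution is 33.02 per arm, rounded up to 34, or 68 in total. This matches the stated 68 before any attrition allowance. With 20% attrition, the two-sided total would be 83 to 86, depending on the formula and rounding. A one-sided calculation with attrition gives 26/0.8 = 32.5, so 33 per arm and 66 in total. That discrepancy is a separate matter. Here the figure only supplies the arm size: 68/2 = 34, assuming 1:1 allocation (the ratio is not stated), and 34 × 0.8 ≈ 27 after 20% attrition.

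**2. Model.** Let both arms have the same true mean change, so there is no intervention effect. Express that change as δ, in SDs of the individual changes. The documents give no value for δ, so a range is shown. Let p(δ, n) be the chance that a two-sided paired t test at .05 is significant in one arm of size n. The arms are independent, so:

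- P(significant in the intervention arm only) = p(1 − p)
- P(significant in exactly one arm) = 2p(1 − p)

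Since p(1 − p) is largest at p = 0.5, the first cannot exceed 0.25 and the second cannot exceed 0.50.

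**3. Results.**

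| δ | n per arm | p | Intervention arm only | Exactly one arm |
|---|---|---|---|---|
| 0 | 34 | 0.050 | 0.048 | 0.095 |
| 0.2 | 34 | 0.205 | 0.163 | 0.326 |
| 0.35 | 34 | 0.509 | 0.250 | 0.500 |
| 0.5 | 34 | 0.808 | 0.155 | 0.311 |
| 0.8 | 34 | 0.995 | 0.005 | 0.010 |
| 0 | 27 | 0.050 | 0.048 | 0.095 |
| 0.2 | 27 | 0.170 | 0.141 | 0.283 |
| 0.35 | 27 | 0.418 | 0.243 | 0.486 |
| 0.5 | 27 | 0.706 | 0.208 | 0.415 |
| 0.8 | 27 | 0.979 | 0.020 | 0.041 |

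For example, at δ = 0.2 and n = 34: 0.205 × (1 − 0.205) = 0.163.

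**4. Comparison.** In 50,000 simulated trials per setting (δ = 0, 0.35 and 0.5; n = 34 and 27), a between-arm t test on the change was significant in 4.9% to 5.0% of trials. The common change cancels. The simulated one-arm-only rates agreed with the formula, for example 25.1% for the intervention arm only at δ = 0.35 and n = 34.

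**5. Where a baseline exists.** The Outcomes section gives T0 values for BP, medication adherence (Morisky scale), physical activity time, and the cardiovascular and body composition indicators in both arms. Learning performance is measured at T0 and T1 only, dietary adherence at T1 and T2 only, and satisfaction and acceptability at T1 in the intervention group only. For BP monitoring adherence, T0 is stated for the control group, while the intervention group is described as measured weekly until T1. The weekly exercise adherence ratio is described for the intervention group only.

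**The case against.** The strongest reply is that the randomised comparison is already there. The sentence before the paired tests plans between-arm tests at all three time points, the sample size is built on a between-group effect, and the Introduction aims to assess effectiveness in two groups. This stands. A reader might infer that the trial will be analysed as two single-arm studies, or that efficacy will be declared when one arm is significant and the other is not. The document states neither, and the wording in the Results section is an expectation, not a success criterion.

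The phrase limiting the paired tests to some outcomes also has an innocent reading, since step 5 shows that not every outcome has a baseline. A reader might infer selective reporting from it, but the text does not support that. Naming the outcomes is also the kind of detail that a fuller plan may hold.

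Finally, the size depends on an assumed common change. The 25% is a mathematical ceiling, and with no common change the figure is about 5%. When both arms truly change, a significant paired test is a correct finding of change, and it misleads only if read as an effect of the intervention.

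What the reply does not remove is that the stated text puts both families under one P rule with no ranking, offers no between-arm analysis of change, and words the expected result as change.

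**Conclusion.** The point holds in a limited form. The plan has a randomised comparison, but it is unadjusted at each time point, and the only stated analysis of change is a set of non-randomised paired tests of equal standing. If both arms change equally, with 34 per arm and two-sided tests, significance in the intervention arm alone occurs in about 5% to 25% of trials, depending on the common change. The rate falls again for large changes, when both arms are nearly always significant. With 27 per arm the range is similar. These figures rest on 1:1 allocation, normally distributed changes with equal SD in both arms, and a common change that the documents do not quantify. They show how little a one-arm P value says about the arm difference, and they do not predict this trial's error rate.

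**What to change.** - **Efficacy.** State that efficacy conclusions rest on the between-arm difference at T1 and T2, with 95% CI, adjusted for the T0 value where one is collected: BP, medication adherence, physical activity time, and the cardiovascular and body composition indicators. Include BP monitoring adherence if both arms have T0. For learning performance, this applies at T1 only.
- **No baseline.** Compare dietary adherence between arms at T1 and T2 without adjustment. Describe outcomes collected only in the intervention group (weekly exercise adherence, satisfaction and acceptability) and draw no comparative claim from them.
- **Within-arm change.** Report it descriptively, as mean change with CI, for every outcome with a T0 value, and label it as not a test of the intervention.
- **Wording.** In the Results section, state the expected result as a difference between arms.

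The data needed are already in the collection schedule. The cost is a little more analysis work and fewer P values to report.

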## Results

The study was funded in December 2021. The WHBDIP trial was approved by the Ethics Committee of Bengbu Medical College in June 2022 (2022-103) and registered in August 2022 (ChiCTR2200062643). Patient recruitment for those with hypertension started on September 5, 2022, and was completed on September 19, 2022. The 3-month intervention and phased data collection were completed in January 2023. Data analysis will commence in August 2023, and the final 1-year health outcome results will be collected in September 2023. We expect the primary outcomes to show changes in adherence indicators during the 3-month intervention, and health outcomes, including BP and other cardiovascular indicators, to change after the intervention and 1 year later. Furthermore, we will report on dropout rates and reasons for dropout during the trial.

## Discussion

The WHBDIP is a WeChat-based digital health program that aims to improve the self-management of BP and promote adherence behavior change among patients with hypertension. If the effectiveness of WHBDIP can be verified, it may be attributed to several key characteristics. First, all interventions were developed based on robust evidence, and we further optimized them. Similar to DASH, a proven effective diet for patients with hypertension, we have created a map of food portions tailored to the dietary characteristics of Chinese people and included beverage options in the scoring table. Second, WHBDIP is a theory-based intervention tailored to patients with hypertension. We specified the target behavior (adherence) and conducted a scientific and systematic procedure to identify the appropriate functions from the 9 behavior functions. We then selected the corresponding BCTs from Michie et al’s [33] taxonomy based on the BCW. These BCTs were compiled into the intervention manual, which will serve as the foundation for the development of the mHealth intervention program. Third, we provided tailored interventions, including intelligent personalized exercise prescriptions and different intervention contents for adherence. For example, people with different movement barriers require different persuasion techniques. Fourth, we provided one-to-one web-based health services, which could increase participant satisfaction. Fifth, this trial involved health-related professionals and followed a community-based telehealth intervention approach. Finally, we designed this trial to meet methodological demands, including adequate power, allocation concealment, and necessary blinding.

If the WHBDIP is proven to be effective, it could be integrated into the upcoming eHealth promotion program. We will develop community-based apps to promote the management of patients with hypertension, including patient terminals and health service provider terminals. The app will deliver personalized e-interventions, such as reminders, videos, and other content, to patients through specific logic that incorporates behavioral change techniques. This will enable the manual intervention to be automated. It may serve as an alternative, convenient, and cost-effective approach, deserving further experimental verification, for doctors and nurses in primary health care institutions to provide tailored and consistent health services for patients with hypertension.

The study has some limitations. First, due to the nature of the intervention, interventionists in this trial cannot be blinded. To reduce the impact, we provide detailed training and an intervention manual to minimize the subjective influence of interventionists. This way, interventions can be standardized as much as possible. Second, some outcome measures rely on patient self-report scales, which may somewhat affect the reliability of the results.

## Abbreviations

BCT: behavior change technique
BCW: behavior change wheel
BP: blood pressure
BPMA: blood pressure monitoring adherence
CVI: content validity index
DA: dietary adherence
DASH: Dietary Approaches to Stop Hypertension
DBP: diastolic blood pressure
EA: exercise adherence
ICVI: item-level content validity index
MA: medicine adherence
mHealth: mobile health
PAT: physical activity time
SBP: systolic blood pressure
SDGDIS: simplified DASH grading diet index score
WHBDIP: WeChat-based health behavioral digital intervention program
